#### Control group

The control group will not have any type of intervention; they will be asked to continue with their normal life habits. At the end of the study, participants will be invited to participate in a physical activity program at their workplace.

#### Follow up of participants

For the C-P group, the computer application will record the number of times the breaks will be accepted, rejected, or postponed, and it will generate a weekly summary. Furthermore, a member of our research group will consistently make phone calls to ensure that everything remains in order. In the case of the B-B group, all sessions will be recorded, with attendance tracking for all participants. Meanwhile, for the control group, a research group member will periodically remind them of the recommendations provided at the beginning of the 12 weeks. After the intervention, participants will be compensated by receiving a report with the values provided by accelerometry and a complete report of their body composition from the DXA measurements. There will be no monetary compensation. In addition, to qualitatively analyze the participants’ experience with the interventions, general and specific questions will be asked about the performance of the breaks (C-P and B-B). These questions will be asked in a private questionnaire format so as not to influence the answers of the participants. These results will be analyzed as a secondary objective in order to identify barriers and facilitators to be considered in future studies. For more information on these questions consult Supplementary material.

In case of desertion for any reason (i.e., leaving the country, change of job, impossibility of measurements), a sensitivity analysis will be performed with and without intention to treat. It is important to note that the exercise protocol was based on previous recommendations by Chilean governmental organizations, and that the protocol is designed to pose little or no risk to the health of the participants. However, in case of any type of injury risk, the participants’ institutions have medical insurance that will be effective if necessary.

### Data analysis plan

Owing to the characteristics of the study (i.e., cluster for conformation of the groups), allocation concealment was not possible. However, the blinding of the evaluator is detailed in the study records (more information in ClinicalTrials.gov, identifier: NCT05844267).

Descriptive data from participants will be summarized and presented as means and standard deviations for continuous variables, and frequencies and percentages for categorical variables. Appropriate statistical tests, such as T-tests or Chi-square tests, will be used to determine differences in baseline characteristics and sex differences where applicable. The normality of the variables will be explored using the Shapiro–Wilk test, and visual analysis with Q-Q plots and distribution of residuals will be applied. If the criteria associated with missing at random data are met, the relevance of the imputation will be evaluated.

For our primary outcomes, propensity analysis will be performed. This model allows us to reduce selection bias and strengthen inferences about the causal effect of an intervention in a non-randomized model (79). This analysis aims to balance the characteristics of the groups so that they are comparable in terms of all relevant variables, both known and unknown, that may influence the results. In addition, analysis of variance (ANOVA) or analysis of covariance (ANCOVA) will be applied depending on the objectives of the study. The inter-individual response of the participants will also be analyzed if deemed necessary. For our secondary objectives, we will analyze the possible mediating or moderating roles of our variables. Any additional analysis that the researchers consider necessary will be sought.

In parallel, sensitivity analyses will be performed according to the intention-to-treat principle. All analysis models will also adjust for relevant covariates such as sex, age, socioeconomic status, eating habits, smoking habits among others depending on their relevance in the model studied. To determine which variables are appropriate to use as covariates, directed acyclic graphs will be explored. These graphs are built on the expert knowledge of the researcher, which would facilitate the causal understanding of the phenomenon and the type of linkage between the variables involved, minimizing the introduction of bias during the design of the study and in the analysis of results (80, 81). All analyses will be performed in different software according to the needs of the researchers (e.g., R Studio, Jamovi, SPSS).

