## Methods

### Study design and ethical considerations

“The Up Project” comprises a quasi-experimental study in which the sample will be selected through cluster sampling, with workplaces serving as the basis for establishing both interventions and control groups (ClinicalTrials.gov identifier: NCT05844267). This project has been approved by the Ethics Committee of Pontificia Universidad Católica de Valparaíso (BIOEPUCV-HB 580–2023) and will be conducted following the Declaration of Helsinki and the guidelines of the SPIRITS (Standard Protocol Items: Recommendations for Intervention Trials) checklist (39). Additional information is provided in the Supplementary material. Written consent will be obtained from the participants before beginning and will be guarded and stored by the principal investigators ([name] and CB) to maintain the confidentiality of the participants. All protocol modifications will be communicated and registered on ClinicalTrials.gov.

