### Sample recruitment

Desk-based workers (60 in total) will be recruited voluntarily from universities and educational institutes in the Valparaiso region, Chile. We will extend an open invitation to all desk-based workers of the Pontificia Universidad Católica de Valparaíso (PUCV) in the Faculty of Philosophy and Education and the central office located in the Central Campus. The control group sample will be obtained from Naval Academy’s desk-based workers. It is important to note that the participants of the control group are civilians or retired marines who do not undergo any type of military training or physical tests. Subsequently, our research team will be visiting their offices to conduct face-to-face recruitment. During this process, the participants will be provided a detailed description of the scientific background, research objectives, and safety measures by our research group. We aim to ensure that all participants clearly understand our research and feel comfortable participating in our study. Once accepted, they will be assigned to a group according to the work site. Upon completion of the study, the participants will be given a full report on changes in body composition, physical activity levels, and sedentary time. After the data collection period, the control group will have the opportunity to participate in the same intervention program.

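### The propensity analysis for the primary outcomes is said to balance unknown as well as known variables, which it cannot do, and the control contrasts stay confounded with institution

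*Protocol article*

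**What the plan says.** The Data analysis plan gives the propensity analysis its role: "For our primary outcomes, propensity analysis will be performed". The reason offered is this: "This model allows us to reduce selection bias and strengthen inferences about the causal effect of an intervention in a non-randomized model". The next sentence states its aim, that the groups become "comparable in terms of all relevant variables, both known and unknown, that may influence the results".

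Allocation is described elsewhere. Study design and ethical considerations describes a quasi-experimental study "with workplaces serving as the basis for establishing both interventions and control groups". Sample recruitment says of participants: "Once accepted, they will be assigned to a group according to the work site". On the comparator it says "The control group sample will be obtained from Naval Academy’s desk-based workers", and adds that "the participants of the control group are civilians or retired marines who do not undergo any type of military training or physical tests". Sample recruitment and Booster breaks group (led breaks) together place both intervention arms at the university that employs the principal investigators.

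On adjustment, the last paragraph of the Data analysis plan says "All analysis models will also adjust for relevant covariates such as sex, age, socioeconomic status, eating habits, smoking habits", among others, with the choice guided by directed acyclic graphs. The limitations paragraph of the Discussion names the lack of randomisation first. It does not mention residual or unmeasured confounding, and no section withdraws the statement about unknown variables.

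**The concern.** The sentence credits the propensity score with a property that belongs to randomisation. Randomisation balances measured and unmeasured factors in expectation because assignment is independent of both. A propensity score is estimated from recorded covariates and can be relied on to balance only those. Calling balance on unknowns an aim does not help, because the method cannot meet that aim.

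The design makes this more than loose wording. The primary hypothesis (end of the Background, repeated in the Discussion) is that both interventions do better than control. That comparison sets one employer against another. Perceived stress and occupational pain are self-reported and are listed among the principal outcomes. Workplace culture, workload or affiliation with the investigators' institution could plausibly affect them. If the plan says unknown factors have been balanced, a difference that arises between institutions could be reported as an effect of the breaks.

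**Working it through.** **1. What a propensity score balances.** With measured baseline covariates X, the score is e(X) = P(arm | X). Its balancing property is that, given e(X), the distribution of X does not depend on arm. Nothing equivalent holds for an unmeasured factor U. The covariates named in the Data analysis plan, and any others chosen by directed acyclic graphs, can enter a model only if they were measured.

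**2. Illustration for an unmeasured individual-level factor.** The plan gives no figure for confounding. The only input taken from it is 20 people per group (Sample size calculation: 60 / 3 = 20). That total reproduces as 54 / 0.90 = 60 if the pre/post correlation, which is not stated, is assumed to be 0.5 (test of time) or 0.6 (group-by-time interaction). Nothing below depends on this.

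Assume that X and U, each with SD 1, both differ by 0.5 SD between two sites, with within-group correlation r. In a linear model, once X is balanced, the remaining difference in U is

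d(U) − r × d(X) = 0.5 − 0.5r.

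This was compared with a simulation of inverse-probability weighting on X, 20 v 20, 2,000 runs:

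| r | Formula: difference left in U | Simulated mean difference in U | Share of 0.50 SD left | Runs with difference in U above 0.25 SD |
|---|---|---|---|---|
| 0 | 0.50 | 0.50 | 100% | 80% |
| 0.3 | 0.35 | 0.36 | 72% | 65% |
| 0.5 | 0.25 | 0.25 | 50% | 54% |

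The difference in X itself fell from 0.50 to between 0.01 and 0.02 SD. So weighting works for the measured factor. It helps with the unmeasured one only as far as the two are correlated.

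**3. Institution-level factors.** From Sample recruitment, P(control | Naval Academy) = 1 and P(control | university) = 0. The weight needed for a university employee to stand in as a control would be 1/0, and no such person exists to be matched. Reweighting within arms leaves Naval Academy staff as 100% of the control group and 0% of each intervention group, as before adjustment. Overlap fails by design, whatever covariates the score contains.

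**4. Which contrasts are affected.**

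| Contrast | Institution | Work site |
|---|---|---|
| Booster breaks v control | differs completely | differs |
| Computer prompts v control | differs completely | differs |
| Booster breaks v computer prompts | same | differs |

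The first two rows carry the primary hypothesis.

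**The case against.** The strongest reply is that the authors do not hide the design. The study is labelled quasi-experimental, and the Data analysis plan calls it non-randomised. It speaks of reducing selection bias, not removing it, and words balance as an aim. The lack of randomisation heads the limitations. Covariates are to be chosen with causal graphs, and ANCOVA is already named as an option. All of this stands, and it makes it less likely that a careful reader would be misled. It does not make the statement about unknown variables true, and the limitations paragraph does not say that unmeasured or workplace confounding remains.

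Four stronger readings are tempting, and the documents do not support them.

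- A reader might infer that bias from unmeasured factors is not reduced at all. That holds for institution itself and for factors unrelated to every covariate in the score. Factors correlated with those covariates can be partly balanced, as the table shows.
- A reader might infer that the score will be unstable with 20 per arm, or that matching will discard participants and widen the intervals. The article names neither the covariates in the score nor the method (matching, weighting or stratification), and such detail is commonly left to the analysis plan. Any figure for lost precision would rest on an assumed loss.
- A reader might infer that the propensity analysis should give way to ANCOVA. That is a preference. The plan already allows ANCOVA and covariate adjustment, and neither removes confounding by site.
- A reader might extend the institution argument to all three contrasts. Booster breaks and computer prompts share one institution, so it does not reach that comparison, although their work sites differ.

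**Conclusion.** The point holds in this form. The plan states a property of its primary-outcome analysis that the method does not have, and no section corrects it. For the two contrasts with control, institution coincides with arm, and no score can balance it. The comparison between the interventions is free of that institutional split but is still assigned by work site.

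The size of any bias cannot be derived from the documents. The 0.25 to 0.50 SD left in an unmeasured factor depends on the assumed 0.5 SD site difference and on correlations between 0 and 0.5. It describes imbalance in that factor, not bias in an outcome. The lack of overlap by institution needs no assumption, because it follows from the recruitment rules.

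**What to change.** - In the Data analysis plan, delete *and unknown*, and state that the propensity analysis addresses only measured, individual-level confounding at baseline.
- In the limitations paragraph of the Discussion, say that the contrasts with control are confounded with institution, and that the contrast between the interventions still differs by work site. Limit the causal claim to match.
- Report standardised differences after adjustment, so that readers can see what was balanced.
- Add a sensitivity analysis for unmeasured confounding of the contrasts with control, for example an E-value.

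The cost is a few sentences and a little extra analysis. No new data, change of allocation or change of primary model is required. The downside is a more modest causal claim.

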## Discussion

### Expected results and transfer to the work context

Reducing health problems associated with sedentary behavior is a crucial concern for governments worldwide (82). While several strategies are emerging to mitigate excessive sedentary time in desk-based workers, comprehensive research examining multiple outcomes and protocols is lacking (23, 24, 33). In this context, our study will compare two intervention types (B-B and C-P) that are equivalent in duration and intensity but differ in distribution. In this sense, our primary hypothesis postulates that both intervention groups obtain better results than the control group. However, we do not anticipate significant differences between the intervention groups due to their equal duration and intensity. This design, which is more realistic for future interventions, will allow us to compare (a) the effectiveness of a continuous break protocol versus an interval-based one and (b) the effectiveness of professional-directed pauses versus autonomous breaks directed by a computational application.

Furthermore, this research helps a gap in the literature by concentrating on three pivotal facets of participants’ health. Firstly, we hope that employing DXA for body composition measurement and accelerometry for assessing sedentary and physical activity time could enhance methodological precision in this field. Secondly, we aim to explore effective strategies for enhancing cardiometabolic risk markers in desk-based workers through a more comprehensive and innovative approach. Thirdly, our objective is to contribute to developing evidence-based interventions aimed at diminishing perceived stress levels and occupational pain experienced by workers. Addressing these three indicators could be significant for companies and public health policies. In this line, our hypothesis is that both intervention groups will yield better results compared to the control group.

However, this trial has limitations. First, randomization will not be possible due to the intervention’s characteristics as well as blinded allocation. Second, for the participants’ convenience, compositional measurements were scheduled in the afternoon. This may impact the measurements due to the participants’ hydration and food intake status. Nevertheless, in order to minimize the risk of measurement errors, particularly those related to the time of day, the same measurement protocol will be followed for all participants (83). Third, stress perceived by desk-based workers will be measured through a questionnaire, and exercise intensity will be gaged by RPE. In both instances, it would be desirable to incorporate complementary physiological indicators, such as cortisol levels and heart rate, respectively. Fourth, although the accelerometer allows to determine the sitting and break time, it is not completely appropriate to determine the stationary postures as other devices (e.g., inclinometers) (52). Additionally, our assessment of cardiometabolic risk factors does not encompass a lipid profile.

This study also has strengths to highlight. First, although the OSPAQ, DABQ, and single item of the physical activity questionnaire are not validated in Spanish language, our research group is actively working on these validations in a parallel study. Second, the intervention during 12 weeks already allows to observe behavioral change (44), which could extend in time the effects of the interventions carried out after the study’s end. Thirdly, integrating both device-based and traditional measures for cardiometabolic risk, physical activity, and sedentary lifestyle will enable the creation of a more comprehensive model to understand the effect of two protocols of active breaks at work in our outcomes. In this regard, it is important to remark on the use of DXA for body composition measurements, in contrast to the measures most commonly used in previous studies (i.e., BMI, waist circumference). Fourth, the determination of specific covariates that may affect our outcomes in important ways. These covariates will allow us to adjust our analysis model in order to comprehensively explore the effects of the intervention proposed in this study.

The results of this project can serve as a basis for future interventions, and government and company programs aimed at improving the health of desk-based workers. Promoting these strategies is essential, given that prolonged sitting in the workplace combined with physical inactivity is a crucial risk factor for workers’ physical, metabolic, and mental health.

In summary, “The UP Project” aims to identify effective ways to improve markers of cardiometabolic risk, perceived stress and occupational pain in office workers through breaks aimed at interrupting sedentary time during the workday. We hope that this effort will mark a breakthrough in the search for protocols to improve the health of office workers and contribute with scientific evidence that will contribute to the development of public policies to combat sedentary time.

## Ethics statement

The studies involving humans were approved by Ethics Committee of Pontificia Universidad Católica de Valparaíso (BIOEPUCV-HB 580–2023). The studies were conducted in accordance with the local legislation and institutional requirements. The participants provided their written informed consent to participate in this study. Written informed consent was obtained from the individual(s) for the publication of any identifiable images or data included in this article.
